The *Child Behavior Checklist 1.5-5* (CBCL; [43]) measures social-emotional and behavior problems in infants and young children. It contains 99 brief items describing different behaviors considered potentially problematic for children’s development, including fear to try new things, medically unexplained pain, and defiance, and caregivers indicate on a scale of 0–2 whether these are “*not true*”, “*somewhat/sometimes true*”, and “*very/often true*”. Scores for the 99 items are summed to reach a total problem behavior score. Higher scores therefore in principle reflect more behavioral problems, although somewhat elevated scores still fall within the normative, expected range for infants, toddlers and preschoolers (the average score in a Danish general population sample was 17.3; [50]. It is a validated and widely used instrument: for example, it was able to identify preschoolers with different disorders, particularly externalizing symptoms [51]. The CBCL 1,5–5 has been used for diagnostic purposes in Danish clinical research [52].

The *CDI:Edu* [44] is a Danish short form of the Communicative Development Inventories (CDI; [53], adapted for the childcare setting by replacing vocabulary items unlikely to be used in childcare. The original MacArthur-Bates CDI has been found a valid instrument for measuring receptive and expressive language development from late infancy to toddlerhood [54], and the same holds for its Danish adaptation [55]. The CDI:Edu measures development of the Danish language in children aged 18–36 months and contains 70 vocabulary items; respondents mark words if the child a) understands them, or b) understands and says them. The total number of words marked is the total vocabulary score. It takes about 10 min to complete for one child, which CPs can do in a valid and reliable way: for instance, CDI:Edu scores correlated as expected with gender (girls scoring higher) and maternal educational background (more advanced language development when mothers had more years of formal education), and the items had good internal consistency [44]. In our study, both CPs and parents complete the CDI:Edu. While there is also a Danish short form of the CDI [56], this was developed as a screening tool of language delays in older toddlers, while the CDI:Edu can be used for toddlers of a wider age range.

It is worth noting here that in Denmark, childcare is monolingual: children are exposed only to the Danish language. For children with a different native language (or multiple languages at home), the development of their native language and their secondary/tertiary language (i.e., Danish) may be interconnected, but study findings have suggested this may be a one-way street: stimulation of children’s native language(s) can positively affect learning of their secondary/tertiary language, but not the other way around [57]. We therefore hypothesized that the CIP training would stimulate children’s Danish language development, but would not necessarily affect their vocabulary in another language. We therefore only measure children’s development of the Danish language with the CDI:Edu.

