A combination of high levels of sensitivity and respect for autonomy as well as *structuring and limit setting*, which refers to communicating expectations clearly to children and setting boundaries in a clear and consistent way, matches the profile of an authoritative caregiving style as identified by Baumrind [23], which has predicted long-term positive adjustment in children [e.g., 24].

While the developers of the CIP scales did not base the scales *verbal communication* or *developmental stimulation* directly on Vygotsky´s [25] concept of the zone for proximal development, we acknowledge here there are similarities between Vygotsky´s concept and the assumptions about learning implicit in the scales. The zone for proximal development refers, broadly speaking, to the difference between what children are able to achieve on their own and what they are able to achieve with the guidance of a capable other (adult or peer): the “zone” represents their proximal developmental potential. When CPs talk with children and connect to children´s interests and appropriately challenge their capacities, offering supportive guidance in language and activities, they capitalize on children´s learning potential. Research has shown that children who experienced more speech directed at them, had a larger expressive vocabulary [26, 27]. Also, more developmental stimulation by CPs uniquely predicted increased cognitive development in infants, even when controlling for caregiver sensitivity and children´s earlier cognitive development [6, 28].

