### The present study

In this randomized controlled trial, we test the following research questions:

Does the CIP training enhance the interactive skills of Danish CPs? Based on previous research [9], we hypothesize that CPs who receive the CIP training will improve significantly on the six interactive skills.Does the CIP training enhance the social-emotional and linguistic development of children who are in the care of trained CPs? The effects of the CIP training on the children on childcare has not been evaluated previously, but based on a meta-analysis showing an overall small effect of targeted interventions in childcare on children’s social-emotional development [16], we tentatively expect to find a small positive effect of the CIP training on children’s social-emotional development. Another meta-analysis has shown that when CPs participate in personal development courses or coaching in relation to language, this may have a small or small-to-moderate effect on children’s language development, depending on the measured outcome (small effects for receptive vocabulary and alphabet knowledge, a small-to-moderate effect on phonological awareness; [39]. We therefore tentatively expect small effects of the CIP training on children’s linguistic development.

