### Data analysis

A consequence of the nested structure of our data is that due to similarities within care groups and institutions (e.g. CPs in the group interact with the same children, and may have shared strategies for implementing principles from the CIP training), observations and assessments with different CPs from the same care group or institution are unlikely to be independent from each other. In order to account for this, we will use multilevel modelling to test the effect of the CIP training on CPs’ interactive behavior and on children’s social-emotional and linguistic development. We will test the effect of the CIP training (versus control group) on the six CIP skills using linear regression analyses, adjusting for baseline levels of the CIP skills. We will test the effect of the CIP training (versus control group) on children´s social-emotional and linguistic development using linear regression analyses, adjusting for baseline levels of children´s social-emotional and linguistic development, respectively.

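### The one CDI:Edu score that the article defines is in effect a count of words understood, so it misses words moving from understood to spoken and cannot separate expressive from receptive gains

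*Protocol article*

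**What the plan says.** The CDI:Edu measures Danish vocabulary "in children aged 18–36 months and contains 70 vocabulary items" (protocol article, Secondary outcome measures). On the form, "respondents mark words if the child a) understands them, or b) understands and says them". The scoring sentence follows: "The total number of words marked is the total vocabulary score". No other CDI:Edu score is named in the article. The same section describes the parent instrument as a "valid instrument for measuring receptive and expressive language development from late infancy to toddlerhood". Both parents and childcare providers fill in the form.

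The evidence behind the language outcome is mixed. Under Theoretical foundations and assumptions of the CIP scales, the article cites research that "children who experienced more speech directed at them, had a larger expressive vocabulary". Under The present study, the expected effect comes from a meta-analysis with "small effects for receptive vocabulary and alphabet knowledge, a small-to-moderate effect on phonological awareness", and the hypothesis reads "We therefore tentatively expect small effects of the CIP training on children’s linguistic development". The Data analysis section plans linear regression in a multilevel framework, "adjusting for baseline levels of children´s social-emotional and linguistic development, respectively", with no mention of a split between words understood and words said.

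**The concern.** The form records two levels of knowledge for each word, and the stated score gives both the same weight. Since the second level includes the first, adding them gives the number of words understood. Whether the child says the word makes no further difference.

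The hypothesis concerns linguistic development generally, and speaking is part of that. If the training mainly helped children to say words they already understood, this score would not show it. If it helped both understanding and speaking, the score would show only part of the gain. A non-significant result could then be reported as no effect on linguistic development when only the receptive side had been tested. Preliminary checks plans Bayes Factors for non-significant findings, so such a result might even be presented as support for the null hypothesis.

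**Working it through.** The article gives no figure that depends on this scoring rule, so there is none to reproduce. The stated child-outcome power (0.80 for an effect size of 0.26, Power analysis) is unaffected. The check is to apply the stated rule to possible changes on the form.

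**Inputs from Secondary outcome measures:** 70 words; two ways to mark a word; score = number of words marked.

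**Notation:** a = words marked as understood only; b = words marked as understood and said; a + b ≤ 70.

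- Defined total: T = a + b, which is the number of words understood.
- Words said: S = b.

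**Extremes.** With a = 70 and b = 0, T = 70. With a = 0 and b = 70, T = 70. The two children have the same total, while S is 0 for one and 70 for the other.

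**One word at a time.**

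- Understood to said: Δa = −1, Δb = +1, so ΔT = 0 and ΔS = +1.
- Unmarked to understood and said: Δb = +1, so ΔT = +1 and ΔS = +1.
- Unmarked to understood only: Δa = +1, so ΔT = +1 and ΔS = 0.

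**Worked illustration.** The counts are assumed, not taken from the article. Start at a = 30, b = 20, so T = 50 and S = 20.

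| Change by follow-up | a, b after | T | S |
|---|---|---|---|
| 10 words from understood to said | 20, 30 | 50 → 50 | 20 → 30 |
| 10 words from unmarked to understood and said | 30, 30 | 50 → 60 | 20 → 30 |
| 10 words from unmarked to understood only | 40, 20 | 50 → 60 | 20 → 20 |
| 10 from understood to said, 5 from unmarked to understood only | 25, 30 | 50 → 55 | 20 → 30 |

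The total misses the gain in row 1. It gives rows 2 and 3 the same value although one is a gain in speech and the other is not. In row 4 it shows 5 points where words said rose by 10.

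Baseline adjustment does not recover this. If T is the same before and after, as in row 1, conditioning on the earlier T leaves the spoken gain outside the model.

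The size of the loss in the trial depends on how many words are understood but not said at baseline and how many of them become spoken. The article gives neither.

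**The case against.** Four points can be made for the plan.

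1. *Spoken gains are not lost altogether.* A reader might infer that the score cannot register gains in spoken words at all. The rule does not support that: a word going from unmarked to understood and said adds a point. What stands is narrower. The point comes from the word now being understood, and the step from understood to spoken adds nothing.

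2. *The rationale is not purely expressive.* A reader might infer that the plan justifies its language outcome by expressive vocabulary and then fails to measure it. The expressive evidence sits in the background to the caregiver scales. The formal hypothesis rests on a meta-analysis in which the only vocabulary effect named is receptive. A receptive count is therefore a legitimate outcome here. It is still only part of what a hypothesis about linguistic development covers.

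3. *The sentence may be a condensed instrument description.* It does not say that no other score will be derived, and the article promises pre-registration of all analyses before data analysis starts. So it cannot be claimed that the expressive data are collected and then discarded. On the other side, the same section does name two scores for the SDQ (total difficulties and prosocial), where two are meant. For the CDI:Edu it names one.

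4. *Putting words said first would be a preference.* This is accepted. Nothing in the article obliges the trial to rank expressive above receptive vocabulary.

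**Conclusion.** The point holds in a limited form. As defined, the CDI:Edu total is a count of words understood. It gives exactly 0 for each word moving from understood to spoken, and it cannot tell expressive from receptive gains. This follows from the scoring rule and needs no outside data on the instrument.

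It rests on one assumption: that the stated total is the score to be analysed. If the pre-registration already includes a words-said score, the point is met. The practical loss cannot be quantified from the article. The matter concerns a secondary outcome and is an inexpensive improvement to the plan; it does not threaten the primary analysis.

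**What to change.** From the same form, derive two scores: words understood (a + b, the current total) and words said (b). In the planned pre-registration, specify for each a multilevel model adjusted for its own baseline value, and state in advance how the two results will be read together. Words said need not be the leading score.

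The cost is one derived variable and one further model per informant. With parents and childcare providers analysed separately, that is 1 × 2 = 2 extra secondary tests, to be counted in any multiplicity handling. No new data are needed.

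If the authors prefer to keep the single total, they should call it receptive vocabulary and limit the conclusion to that, including any Bayes Factor statement after a non-significant result.

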### Power analysis

The current study is a 3-level clustered randomized trial (CRT): CPs (level 1) are nested within care groups (level 2), which are nested within childcare centers (level 3). The multilevel nature of CRTs requires special consideration when doing power calculations. In order to detect main effects of the CIP training, maximizing the number of units at level 2 and especially 3 will benefit statistical power more than maximizing the number of individuals at level 1 [58]. In order to detect effects of level 2- or 3-moderators (for instance, ESCS index of the childcare center, a level 3-moderator), CRTs generally need many more clusters than for main effects, and moderating effects are typically smaller than main effects, so that testing for level 2- or 3-moderators is often financially and practically unfeasible [58]. However, in order to detect moderators at level 1, maximizing the number of individuals within clusters benefits power most [58]. We have determined our sample size at level 1, 2 and 3 by calculating the minimally detectable effect size (MDES) for main effects of the CIP training on CPs´ interactive skills and children´s social-emotional and linguistic development. In these considerations we also had to strike a balance between investing resources toward training CPs in as many childcare centers (units at level 3) as possible to achieve high statistical power for analyses on our primary outcome measures (CPs’ interactive skills), while also including enough CPs within each care group (level 1) so that the children in the group might benefit more from their CPs´ training, leading to larger training effects on child development.

In order to balance our investment of resources on maximizing training effects on CPs´ interactive skills (by striving for recruitment of CPs from as many childcare centers as possible) and on maximizing training effects on child development (by training as many CPs in each care group), we decided to include a maximum of 2 CPs per care group. Some center leaders only want 1 CP per care group to participate, presumably due to difficulties arranging for alternative staff during training hours (despite the City of Copenhagen financing alternative care). Therefore, per care group, 1–2 CPs participate in the study. Through power calculation in PowerUp! (see https://www.causalevaluation.org/power-analysis.html; [59]), we estimated that with an average of 2 CPs per care group, 3 care groups per childcare center, and a total of 35 childcare centers, we will have a power of 0.84 at (*α* = 0.05) to detect an MDES of 0.35, which was the average ES in a meta-analysis of RCTs testing different trainings on CPs’ interactive quality [15]. In the first RCT of the CIP [9], which came out after the above meta-analysis, the ES for *structuring & limit setting* was also 0.35, while the other effects were larger: 0.59–0.79.

Because childcare interventions focused on improving process quality do not directly target child outcomes, the effects of these interventions on children tend to be smaller (overall ES of 0.26 in [15]). We estimated that with an average of 5 children per care group, 3 care groups per childcare center, and a total of 35 childcare centers, we will have a power of 0.80 to detect an ES of 0.26.

### Data analysis

A consequence of the nested structure of our data is that due to similarities within care groups and institutions (e.g. CPs in the group interact with the same children, and may have shared strategies for implementing principles from the CIP training), observations and assessments with different CPs from the same care group or institution are unlikely to be independent from each other. In order to account for this, we will use multilevel modelling to test the effect of the CIP training on CPs’ interactive behavior and on children’s social-emotional and linguistic development. We will test the effect of the CIP training (versus control group) on the six CIP skills using linear regression analyses, adjusting for baseline levels of the CIP skills. We will test the effect of the CIP training (versus control group) on children´s social-emotional and linguistic development using linear regression analyses, adjusting for baseline levels of children´s social-emotional and linguistic development, respectively.

### Preliminary checks

Trials like the current one, especially with data collection taking place over an extended period of time (around 5 months for each data collection cycle, see Fig. 1), are liable to drop-out of participants. We will evaluate the randomness (vs. systematicness) of missing data. In order to maintain the original random allocation of (CPs and children within) care groups and counter potential biases in analyzing training effects, we will use an intent-to-treat approach in our analyses, by which the data of participants (CPs and children) who dropped out are analyzed as if they had completed the study, for instance through multiple imputation of missing outcome data [60].

Adjusting for covariates that help explain some of the variation in outcomes between participants can increase statistical power in randomized trials, yet is not commonly done [61]. Indeed, interventions trials in childcare similar to this one often do not report including covariates, apart from baseline levels of the outcome measure. It is therefore difficult to determine based on previous literature what covariates might enhance precision of estimation. We will evaluate the relevance of potential covariates to determine whether they should be included in the main analyses, including whether CPs did their training individually or in pairs, the caregiver-child ratio (number of caregivers per child) in the care groups during the video recordings, CPs´ educational background, and whether CPs in the control group had participated in any alternative training during the data collection period. For analyses of training effects on child development, we will test children´s age and the hours they spend in childcare per week as potentially relevant covariates. We will check if they (a) differ between the training and control group, and (b) are associated with the outcome. Covariates will be retained if they correlate ≥ 0.70 with the outcome, independently of whether they differ between the training and control group; they will be eliminated if they correlate ≤ 0.30 with the outcome; if they correlate 0.31-0.69 with the outcome, they will be retained if they are imbalanced between the training and control group [62]. For transparent publication and future meta-analytic purposes, we will report both unadjusted and adjusted models. In the case of non-significant findings, we will calculate Bayes Factors to indicate whether the null hypothesis or the alternative hypothesis predicts the data better, or whether the data cannot distinguish clearly between the null and alternative hypothesis [63, 64]. Before data analysis starts, all analyses will be pre-registered on the Open Science Forum (see https://osf.io/5fcs2/).

## Discussion

This trial evaluates whether the CIP training, which was found effective in improving the CPs’ interactive skills in a Dutch context [9], is effective in the Danish childcare setting. We expand on the original Dutch trial by also looking at potential positive effects on children’s social-emotional and linguistic development. If indeed the training leads to a childcare environment in which children are met with more sensitivity, respect for their initiatives and perspectives, a clearer structure, and more positive interactions with peers, then we expect this, based on developmental theory and research, to boost their social-emotional development. We expect that more frequent and high-quality verbal communication will affect children´s language development positively.

Many intervention trials in childcare are underpowered [15], because detecting the aggregate moderate (for caregivers) or small (for children) intervention effects requires very large samples which is generally extremely time consuming and labor intensive due to delivering of the interventions and coding observational measures. Our randomized trial aims to have a larger sample and therefore more statistical power than the studies included in the meta-analysis by Werner and colleagues [15]. This makes it feasible for us to detect the effects found by Werner and colleagues ( [15] p.268). Nevertheless there are constraints to the type of analysis we can do while retaining sufficient statistical power. We may therefore not be able to detect factors that affect the CIP training’s success in improving interactive skills in CPs, and in boosting children’s development.

Because we rely on childcare centers’ voluntary participation, we risk that the childcare centers enrolling in the study could do so, for example, because they generally pay attention to and work with child-CP interactions, and may have relatively high process quality already. This means that our sample may not be fully representative, in terms of baseline process quality, of the wider population of childcare centers in Copenhagen and Denmark. Therefore we would not necessarily be able to draw conclusions, based on our findings, applicable to the wider Danish childcare center population. In order to counter this, we keep track of childcare centers’ quality evaluations (conducted by the municipality) to make sure we don’t over-recruit childcare centers with evaluations of high quality, and we can steer recruitment toward centers with less positive evaluations as needed. We do the same for centers’ ESCS index, aiming to recruit centers with children of different ESCS backgrounds, as representative as possible of the Copenhagen population.

Additionally, because we recruit at the level of childcare groups, it is possible that participants allocated to the waiting-list control group benefit from the CIP training before taking part in it, either because (despite our request not to do so) participants in the CIP training group discuss training content with their colleagues, or because they show improved interactive skills and their behavioral change is observed by their colleagues in the waiting-list control group. When recruiting and at the start of each CIP training, we stress the importance of not discussing training content with colleagues in the control group until data collection is over.

Sensitive and stimulating interactions are crucial for the development of all children in child care, and can have a protective effect for children who may experience more adversity at home [7, 65]. Because interactions between CPs and children in more than a third of Danish nurseries have been found of insufficient quality in recent research, identifying effective interventions that can improve CP´s interactive skills is a priority in Denmark. If we found that the CIP training can be effective in the Danish context, this would be an important first step toward implementing training in these six interactive skills in Danish childcare. Additional research to evaluate whether the CIP training is effective for interactions with older children (4–5 years) would be necessary. Should the CIP training prove effective, we will evaluate the feasibility of integrating the CIP training in the Professional Bachelor Program in Social Education (which educates future CPs) at University College Copenhagen. In our view, it is of vital importance that future CPs get targeted behavioral training in interacting with infants and young children in a sensitive and stimulating way.

